**ABBREVIATIONS LIST**

| Abbreviation | Text                                         |
|---------------------|-----------------------------------------------------|
| ADME                | absorption, distribution, metabolism, and excretion |
| AE                  | adverse event                                       |
| AFB                 | acid-fast bacilli                                   |
| AI                  | Associate Investigator                              |
| ALT (SGPT)          | alanine transaminase                                |
| AST (SGOT)          | aspartate transaminase                              |
| AUC                 | area under the curve                                |
| β-hCG               | human chorionic gonadotropin                        |
| BAL                 | bronchoalveolar lavage                              |
| BCG                 | bacillus Calmette-Guérin                            |
| CC                  | Clinical Center                                     |
| CFP10               | Culture Filtrate Protein 10                         |
| CFU                 | colony forming unit                                 |
| CI                  | confidence interval                                 |
| CNS                 | central nervous system                              |
| CRF                 | case report form                                    |
| CSF                 | cerebro-spinal fluid                                |
| CV                  | curricula vitae                                     |
| DHHS                | Department of Health and Human Services             |
| DIR                 | Division of Intramural Research                     |
| DSMB                | Data and Safety Monitoring Board                    |
| DST                 | drug susceptibility testing                         |
| DTP                 | days to positivity                                  |
| DVD                 | Digital Versatile Disc                              |
| EKG                 | electrocardiogram                                   |
| ELF                 | epithelial lining fluid                             |
| ELISA               | enzyme-linked immunosorbent assay                   |
| EOT                 | End of Therapy                                      |
| ESAT-6              | Early Secretory Antigenic Target 6                  |
| FDA                 | Food and Drug Administration                        |
| FDG                 | [  F]-fluoro-2-deoxy-D-glucose         |
| GCP                 | Good Clinical Practice                              |
| HIV                 | human immunodeficiency virus                        |
| HRCT                | high-resolution computed tomography                 |
| ICH                 | International Conference on Harmonisation           |
| IFN-γ               | interferon gamma                                    |
| IMS                 | Imaging Mass Spectrometry                           |
| INH                 | Isoniazid                                           |
| IRB                 | institutional review board                          |
| ITRC                | International Tuberculosis Research Center          |
| IUD                 | intrauterine device                                 |
| IV                  | Intravenous drug administration                     |
| KM                  | Kanamycin                                           |

| Abbreviation | Text                                                  |
|--------------|-------------------------------------------------------|
| ADME         | absorption, distribution, metabolism, and excretion   |
| LCID         | Laboratory of Clinical Infectious Diseases            |
| LCMS         | liquid chromatography-mass spectrometry               |
| MALDI        | Matrix-assisted laser desorption/ionization           |
| MCV          | mean corpuscular volume                               |
| MDR-TB       | multi-drug resistant tuberculosis                     |
| MIC          | Minimum inhibitory concentration                      |
| MBC          | Minimum bactericidal concentration                    |
| MPC          | Mutation prevention concentration                     |
| MOHW         | Ministry of Health and Welfare                        |
| MS           | Mass Spectrometry                                     |
| MTA          | Material Transfer Agreement                           |
| MTB          | Mycobacterium tuberculosis                     |
| NIAID        | National Institute of Allergy and Infectious Diseases |
| NIH          | National Institutes of Health                         |
| NITD         | Novartis Institute of Tropical Diseases               |
| NLME         | non-linear mixed effects                              |
| OFX          | Ofloxacin                                             |
| OHRP         | Office for Human Research Protections                 |
| OHSR         | Office of Human Subjects Research                     |
| PBMCs        | Peripheral blood mononuclear cells                    |
| PD           | Pharmacodynamics                                      |
| PI           | Principal Investigator                                |
| PK           | Pharmacokinetics                                      |
| PO           | Oral drug administration                              |
| PZA          | Pyrazinamide                                          |
| qd           | Once daily                                            |
| RBC          | red blood cell                                        |
| RCA          | Research Collaboration Agreement                      |
| RIF          | rifampin or rifampicin                                |
| SAE          | Serious adverse event                                 |
| SM           | Streptomycin                                          |
| SOC          | Standard of Care                                      |
| SPSS         | Statistical Package for Social Sciences               |
| SUV          | Standardized Uptake Value                             |
| TB           | tuberculosis                                          |
| TBRS         | Tuberculosis Research Section                         |
| TST          | Tuberculin Skin Test                                  |
| ULN          | upper limit of normal                                 |
| US NRC       | United States Nuclear Regulatory Commission           |
| WBC          | white blood cell                                      |
| WHO          | World Health Organization                             |
| XDR TB       | Extensively Drug-resistant Tuberculosis               |

## 1. Précis – Abstract

It takes 6 to 24 months of intensive combination therapy to cure tuberculosis (TB) with antibiotics that have proven activity in vitro. In contrast, many pulmonary infectious diseases can be cured following single drug treatment with similar drugs for only one to a few weeks. We hypothesize that the unusual complexity of TB lesions and the degree of sequestration of TB bacilli within these lesions may limit access of the drugs to their site of action, leading to treatment failure, long treatment duration and the emergence of drug resistance. To test the hypothesis that drug maldistribution into lesions impacts on treatment duration and failure, we propose to examine the lesion-specific penetration properties of 5 standard anti-TB drugs in the lungs of subjects selected for lung surgery. The study is designed to understand what lesion types are the most difficult to penetrate. This aspect of TB drug pharmacokinetics has been largely neglected so far, probably owing to the lack of adequate technology and the limited availability of human TB lesion samples. Fifteen patients who elect lung resection surgery will be asked to participate in the study. Consented subjects will receive 5 first and second line anti-TB drugs concomitantly at 1 of 5 pre-determined times prior to surgery. At the time of resection, drug levels will be measured in plasma, in uninvolved lung tissue and in lesions using standard analytical methods as well as imaging Mass Spectrometry (MS) where drug concentration gradients can be visualized across tissue sections. The major aim of this study is to determine actual concentrations and permeability coefficients of the 5 study drugs in various lesion types contained within subjects' surgically removed lung tissue. Data analysis will also provide the **relative exposure** of each drug in plasma versus lung tissue and lesion. If conclusive, the results may be taken into consideration when selecting drug doses and dosing regimens. Additionally, images generated by standard of care (SOC) High Resolution Computed Tomography (HRCT), and Dynamic MRI for each subject will provide information regarding lesion structure and anatomy, lesional blood flow and microvascular function. Lesion-specific correlations will be established between CT radiology and drug pharmacokinetic (PK) to identify which histopathologic lesion types may be particularly difficult to sterilize and to evaluate the potential impact of drug penetration on treatment outcome. The long term goal of this study is to identify the factors behind poor lesion penetration, so that new agents can be optimized with better penetration properties to target 'harder-to-sterilize' lesion types.

## 2 Study Objectives

### 2.1 Primary Objective

The primary objective of this study is to compare the relative penetration efficiency of RIF and KM for large caseous necrotic nodules versus uninvolved lung, contained within surgically removed lung tissue of subjects receiving these drugs prior to lobectomy.

### 2.2 Secondary Objectives

- 1) To determine the absolute penetration efficiency of each of the five drugs in uninvolved lung tissue and in closed necrotic lesions and cavities
- 2) To compare the penetration of RIF, INH, PZA, MXF and KM into closed caseous necrotic lesions versus open cavities
- 3) To compare the levels of RIF and KM in plasma versus caseous necrotic lesions over time
- 4) To compare the levels and exposure of all study drugs in plasma, normal lung and lesions

## Measurement of Anti-TB Drugs in Lung Tissue From Patients Having Surgery to Treat Tuberculosis

- 5) To calculate classical PK/PD indices in plasma and lesions, in relation to minimum inhibitory concentration (MIC), minimum bactericidal concentration (MBC) and mutation prevention concentration (MPC), for future regimen optimization
- 6) To correlate lesion concentrations of the 5 study drugs with lesion type, as determined by histopathology and HRCT, and to identify lesion-specific patterns of drug penetration kinetics
- 7) To correlate lesion concentrations of the 5 study drugs within each lesion type, and to identify drug-specific patterns of penetration kinetics
- 8) To correlate lesion type and structure, as determined by histological microscopic analysis, with radiologic images

- 9) To visualize and quantify concentration gradients of the five study drugs within the different layers of closed lesions, using scanning mass spectrometry across tissue sections
- 10) To assess vascular structure, endothelial function and perfusion around individual lesions, using Dynamic (contrast enhanced) MRI

### 3 Study Design and Methods

#### 3.1 Design

This is a single-dose pharmacokinetic study of 5 concomitant drugs where resected lung tissue will be recovered to determine and compare drug levels within plasma, sputum, healthy lung and pulmonary TB lesions over a 24h period. Comparison and modeling of the concentration-time profiles in plasma and lesions are used to infer permeability coefficients, exposure ratios and concentration gradients for five major 1st and 2nd line TB drugs: RIF, INH, PZA, KM and MXF. Subjects will be randomized to receive the 5 drugs at one time point, either at 2, 4, 8, 12 or 24h prior to surgery, or as close as practical to those times with careful recording of the time of administration. Enrollment will continue until evaluable tissues from 3 subjects have been processed at each assigned time point. Blood and sputum samples will be obtained just before drug administration (trough), and blood samples will also be obtained at 2h ( $C_{max}$ ) and 6h post-dosing or as practicable. Whenever possible, one additional blood and/or sputum sample will be obtained between drug dosing and surgery. Finally, blood will be collected at the time of central line placement and sputum at the time of intubation prior to surgery. The time of each blood draw and sputum collection will be recorded as carefully and accurately as possible. Urine will be systematically collected between the time of drug administration and surgery. The removed tissue will be dissected to separate lesion material from uninvolved lung. The location of each lesion within the lung lobes will be recorded. Each lesion will be measured and weighed, then further divided to perform the following analyses: determination of overall lesional drug concentrations by liquid chromatography-mass spectrometry (LCMS), imaging mass spectrometry and histopathology analyses to visualize 2D drug distribution within lesions. A pre-operative dynamic MRI scan (30-60 min duration) will be conducted one to two weeks prior to surgery to assess lesional perfusion and endothelial function. This procedure can be performed with most MRI machines in clinical use and this may be taken at a different site. A scan will be obtained before injection of the contrast agent (gadolinium). After the contrast agent is given, the subject will be scanned serially at several time points up to 8 minutes post-injection. The rate of gadolinium uptake and its retention properties will be determined using software. The entire scan will take about 45 minutes. A subject will participate in this study from entry (1 to 2 weeks prior to surgery), through surgery and for 48h post surgery.

#### 3.2 Population to be Studied

The study population will be drawn from subjects with pulmonary tuberculosis who elect to undergo lung resection at (i) the Asan Medical Center, Seoul, (ii) Pusan National University Hospital, Busan, Republic of Korea, and (iii) National Medical Center, Seoul, Republic of Korea.

#### 3.3 Treatment Regimen and Treatment Period(s)

Five groups of 3 subjects will each receive one concomitant dose of all 5 study drugs according to the doses and routes presented below. Study drugs will be administered 2, 4, 8, 12 and 24h prior to surgery. For subjects who will be on one or more of the study drugs as part of their

ongoing treatment regimen, the time of administration will be adjusted to meet the requirements of the study design. For subjects whose drug regimen already contains an aminoglycoside other than KM, this aminoglycoside will be substituted with KM, provided that the subject consented to the substitution.

### Doses:

- Rifampicin (RIF) will be dosed orally at 600mg or 450mg for subjects under 50kg of bodyweight;
- Isoniazid (INH) will be dosed orally at 300mg;
- Pyrazinamide (PZA) will be dosed orally at 1.5g;
- Moxifloxacin (MXF) will be dosed orally at 400mg;
- Kanamycin (KM) will be dosed intramuscularly at 1g or 750mg for subjects under 50kg of bodyweight

The 5 groups of subjects are distinguished by the timing of the drug administration, determined by randomization. The timing will be one of 24, 12, 8, 4, and 2 hours prior to estimated vessel and bronchus ligation time, which takes place at varying times after the start of surgery, depending on the extent of adhesions between the pleural membrane and the lung lobes. These times may vary slightly due to constraints inherent to the surgical procedure. Therefore, the exact timing of vessel and bronchus ligation relative to drug administration will be recorded accurately. Ligation marks the time of isolation between tissue compartment and plasma compartment, and will therefore be used as the time post-dosing in the PK analysis.

We will allow the following deviations from assigned timing between drug administration and vessel ligation:

- minus 1h and plus 3h for the 2h group
- minus 2h and plus 4h for the 4h group
- minus 4h and plus 6h for the 8h group
- plus or minus 6h for the 12h group
- plus or minus 12h for the 24h group

In cases where these maximum deviations are exceeded, samples will be collected and analyzed for drug content, but the data will be marked as falling outside allowable time points. To compensate for these potential fall-outs, enrollment will continue until evaluable tissues from 3 subjects falling within the allowable window are obtained in each group. Two statistical analyses will be conducted, one including only those subjects in compliance with the protocol, and one including all subjects. Both sets of results will be interpreted in light of the cause(s) for delay.

### 3.3.1 Study Schema

[figure not shown]

### 3.3.2 Study Time Line

#### Within 14 days prior to surgery

- Consent
- Pregnancy test if female
- Randomization
- Dynamic MRI to quantify lesional perfusion and endothelial function

#### Two weeks to one day prior to surgery

- Sputum collection for bacteriological analysis

#### 24h to 2h prior to surgery

- Subject will receive the 5 study drugs **once**, as shown below.
- Doses:
  - RIF 600mg PO (450mg if <50kg);
  - INH 300mg PO
  - PZA 1.5g PO
  - KM 1g IM (750mg if <50kg)
  - MXF 400mg PO

**Drug administration:** 24, 12, 8, 4, or 2h (as randomized) prior to estimated vessel and bronchus ligation time, which takes place at varying times after the start of surgery, depending on the complexity of the surgical procedure (see section 4.3 above for allowable deviations from assigned time points). For subjects whose drug regimen already contains an aminoglycoside other than KM, this aminoglycoside will be substituted with KM, provided that the subject consented to the substitution.

**Blood sampling for PK:** just prior to drug administration, 2h post-dosing (except for group 5), 6h post-dosing (except for group 4 & 5), at anytime between drug dosing and surgery (optional), at the time of central line placement and at the time of vessel and bronchus ligation. While exact timing of sampling can deviate from the recommended time points, accurate recording of the sampling time is critical to the success of the study.

**Sputum sampling prior to surgery:** Sputum will be collected immediately before drug administration (1 mL or more) with accurate recording of each production time, only if the subject is productive. One additional sputum sample will be collected at any time between drug administration and surgery, with accurate recording of production time.

#### **Urine sampling**

From the time of drug administration to the time of surgery, urine will be collected to determine drug clearance and support PK modeling.

#### **Sputum sampling during surgery**

Sputum will be sampled after endotracheal intubation using a suction catheter with a sputum trap as close as possible to the time of ligation. Optionally, broncho-alveolar lavage (BAL) fluid may also be obtained at the time of ligation by passing a bronchoscope through the endotracheal tube.

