#### ***Dissection of nodules and cavities from resected lung tissue***

The dissection of resected tissue will follow established SOPs for determination of drug concentration in lesions and is described here briefly. All specimen collection tubes are prelabeled and weighed to speed the dissection process.

Prior to surgery, the CT will be reviewed by the pathologist and study team to form a dissection plan. Classes of tissue to be specifically collected are: 1) several regions of apparently normal tissue, 2) large caseous tuberculomas ( $\geq 0.5$  cm), 3) cavity contents, 4) cavity walls including fibrotic tissue layer 6) fibrotic granulomas, and 7) small nodules.

Each lesion collected will be classified, measured for size (length, thickness and depth will be recorded in order to calculate surface-to-volume ratio for PK modeling) and pH, weighed, and recorded on the dissection log describing the disposition of the tissue. All lesions will be divided in this priority as follows and described in the dissection SOP.

- 1) Tissue frozen in liquid nitrogen or dry ice for drug extraction

- 2) Tissue frozen in liquid nitrogen vapor on tissue trays for Imaging Mass Spectrometry and histology
- 3) Tissue in formalin fixation solution for histology
- 4) Any remaining tissue frozen in liquid nitrogen for back-up

All lesions will have at least one sample that may be examined by normal histology methods, including hematoxylin and eosin staining of either formalin fixed or frozen sections. In addition, sections will be stained for acid fast bacilli and CD31 or CD34 (vessels). Larger lesions (0.8 cm or greater) will provide tissue for assessment of bacterial burden, bacterial genome equivalence, bacterial gene expression, and lesion cellular content using standard laboratory procedures.

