### ***Determination of drug levels in uninvolved lung tissue and lesion homogenates by LCMS***

Aliquots of approximately 0.2g (0.1g to 0.25g with accurate recording of the weight to facilitate further processing) of lung and lesion material will be homogenized and processed according to the protocol provided by NITD. Homogenized samples will be mixed with a suitable volume of organic solvent based on indicated weight. The organic phase, containing small molecule drugs, will be evaporated to dryness. These lyophilized samples will be shipped to and analyzed by UMDNJ for the absolute quantification of study drug levels as well as concomitantly administered non-study drugs.

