PZA is completely absorbed orally and only available as an oral drug, with a recommended daily dose of 20 to 25 mg/kg up to 2 grams. No significant effect of concomitant PZA has been observed on the exposure of 1st line TB drugs.

Little is known about the penetration of PZA into tissues. In a study where PZA levels were measured in tuberculous pleural effusion and psoas abscess, intralesional PZA concentrations were 5 to 10-fold lower than serum levels and below the MIC 2h post dose [44]. In contrast, PZA levels in cerebro-spinal fluid (CSF) were similar to those found in plasma, both in rabbits and in humans [45, 46].

**Kanamycin (KM)** is an aminoglycoside antibiotic belonging to the same class of drugs as Streptomycin, one of the first drugs used to treat TB in the 50's. It kills sensitive bacteria by binding to the 30S ribosomal subunit and interfering with protein synthesis. Its MIC and MBC against MTB are 2 and 6 µg/mL, respectively, with a remarkably low MBC/MIC ratio. However, KM is only used to treat serious bacterial infections due to severe renal toxicity and ototoxicity. No interaction with the metabolism of other drugs has been reported. The drug is approved by

the Korean Ministry of Food and Drug Safety (MFDS) but not the US FDA for use against pulmonary TB.

Aminoglycosides do not concentrate effectively in tissues and remain mostly extracellular, in agreement with their hydrophilic nature and low cLogP (Table 1). Accordingly, KM is not orally absorbed and is administered via the intramuscular or intravenous route at a dose of 1g daily or 750mg for subjects under 50kg of bodyweight. The epithelial lining fluid (ELF):plasma ratio of aminoglycosides used against TB ranges from <0.3 for streptomycin to <1.0 for KM. However, receptor-mediated endocytosis of aminoglycosides, by the two main receptors megalin and cubilin found at the surface of epithelial cells, plays an important role in the accumulation of aminoglycosides in renal proximal tubules [47]. Megalin has also been found on the surface of type II pneumocytes, which are critical for the establishment of mycobacterial pulmonary infections as a portal of mycobacterial organisms to the lungs.

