### 5.3 Outcome Measures

#### 5.3.1 Definitions of Terms

- **Caseous necrotic nodule:** closed lesion generally encapsulated with fibrotic tissue, and containing a caseous necrotic center surrounded with multiple cellular layers
- **Cavity:** thick-walled open lesion communicating with an airway and often containing liquefied necrotic material
- **Permeability coefficient (P):** the speed at which a compound moves through a tissue, generally due to diffusion but also to facilitated transport. Its units are cm/sec. In this study, the parameter to be determined for the rate of penetration of a drug to the lesions will be a combination permeability-surface area (PS) coefficient.
- **Penetration ratio:** the ratio between the area under the concentration-time curve in lesion and in blood or  $AUC_{\text{lesion}} : AUC_{\text{plasma}}$  [51].

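### The optional lavage at ligation is neither kept out of the lobe to be resected nor placed after bronchus closure, so it can alter lung and cavity tissue that is then assayed

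*Protocol*

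**What the plan says.** The lavage is permitted by one sentence in section 3.3.2, under sputum sampling during surgery: "Optionally, broncho-alveolar lavage (BAL) fluid may also be obtained at the time of ligation by passing a bronchoscope through the endotracheal tube". Apart from the abbreviation list, BAL appears nowhere else. The design summary (3.1), the dissection, PK and assay text (3.4.2), the endpoints (5.3), the analysis (5.4) and the sample handling text (8.5, 8.6) do not mention it.

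Section 3.3 (Doses) makes the same moment the reference time for tissue: "Ligation marks the time of isolation between tissue compartment and plasma compartment, and will therefore be used as the time post-dosing in the PK analysis".

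Section 3.4.2 lists the tissue to be collected, beginning with "1) several regions of apparently normal tissue, 2) large caseous tuberculomas" and going on to cavity contents and cavity walls. Aliquots of about 0.2 g are then assayed by weight: "Homogenized samples will be mixed with a suitable volume of organic solvent based on indicated weight".

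Section 5.3.1 defines a cavity as a "thick-walled open lesion communicating with an airway and often containing liquefied necrotic material", and a caseous necrotic nodule as a "closed lesion generally encapsulated with fibrotic tissue, and containing a caseous necrotic center surrounded with multiple cellular layers". In section 5.3.2 the primary endpoint divides permeability in diseased tissue by that in healthy tissue. Secondary endpoint 2 in section 5.3.3 compares nodules with open cavities for all five drugs.

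**The concern.** Lavage puts drug-free fluid into an airway and recovers only part of it. Fluid left behind adds mass without drug to a per-weight assay, and fluid sucked back can carry drug away. Under this protocol that may happen at the very instant when tissue concentration is taken as fixed.

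The exposure is selective. Aerated lung and open cavities can be reached through the airway; an encapsulated nodule cannot be reached directly. A ratio of nodule to lung, or of nodule to cavity, would then be shifted in whichever subjects were lavaged. Because the procedure is optional and the protocol does not require its lobe, volume or order to be recorded, the analyst might be unable to identify those subjects later. No analysis can restore a specimen diluted before it was weighed.

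**Working it through.** **1. What the text fixes and what it leaves open.** Sections 3.3, 3.3.2 and 3.4.2 all describe ligation as that of vessels and bronchus. Lavage at that time can mean just before the bronchus is tied, when the specimen is reachable, or after, when a bronchoscope passed through the endotracheal tube cannot reach it. The lobe is equally open. Harm therefore needs four conditions: lavage is done, in the lobe to be resected, before closure, and reaching the pieces later dissected. The protocol neither requires nor prevents this combination.

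**2. Illustrative dilution.** The document gives no lavage figures. Assumptions: 50 to 150 mL instilled, 40 to 60% recovered, 100 to 300 g of tissue reached, density 1 g/mL, even mixing.

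Retained volume r = instilled × (1 − recovered fraction). Fall in concentration d = r / (tissue mass + r).

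- Low end: r = 50 × 0.4 = 20 mL; d = 20 / (300 + 20) = 6%.
- Middle: r = 100 × 0.4 = 40 mL; d = 40 / (200 + 40) = 17%.
- High end: r = 150 × 0.6 = 90 mL; d = 90 / (100 + 90) = 47%.

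**3. The plan's own sample size.** Section 5.2 assumes a 50% difference, SDs of 50% of each mean, zero correlation and 80% power. Two-sided 5% is taken from the 95% interval in section 5.4.1. With means 1 and 0.5, the SD of the difference is √(0.5² + 0.25²) = 0.559. A paired t-test with 12 subjects has power 0.805, and 12 / (1 − 0.20) = 15. Both stated figures reproduce.

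**4. What a lung loss could do to the RIF–KM difference.** As a rough proxy, suppose every subject is lavaged and a fall d in the measured lung level multiplies relative permeability by 1/(1 − d). True values are RIF 1 and KM 0.5 (difference 0.50), or 1 and 1 (no difference).

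| Lung loss, RIF / KM | Observed difference, true 0.50 | Power, n = 12 | Observed difference, true 0 |
|---|---|---|---|
| 10% / 10% | 0.56 | 0.805 | 0 |
| 30% / 30% | 0.71 | 0.805 | 0 |
| 0% / 10% | 0.44 | 0.69 | −0.11 |
| 0% / 20% | 0.38 | 0.52 | −0.25 |
| 0% / 30% | 0.29 | 0.31 | −0.43 |

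For example, 1/0.9 − 0.5/0.9 = 0.56 and 1 − 0.5/0.8 = 0.38. Equal loss stretches means and SDs together, so power is unchanged and no false difference arises when the two values are equal. Only unequal loss creates a false difference or costs power.

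**5. Nodule versus cavity.** Under the same proxy, let lung and cavity both fall by d. The cavity-to-lung ratio is unchanged, while the nodule-to-lung ratio is multiplied by 1/(1 − d). At the middle case that factor is 1 / (1 − 1/6) = 1.20, so the comparison is shifted even when the two exposed tissues are diluted equally.

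**6. Partial uptake.** If only some subjects are lavaged, the average shift is smaller. With 3 evaluable subjects per time point, though, one lavaged subject is a third of the subjects at that time in the pooled fit.

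**The case against.** The strongest reply is that the protocol never directs lavage of the specimen. It leaves the site and volume of an optional sample open, detail that often sits in a procedure manual, and lavage after bronchus closure is already a permitted reading. That is fair, and it makes the harm conditional. It does not remove the point: the plan as written permits a procedure that can change the measured specimen. The SOP cited in section 3.4.2 is described as covering dissection of resected tissue, not bronchoscopy.

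A reader might infer more than the document supports, in three ways.

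- **That lavage biases the RIF–KM contrast against KM.** All five drugs are measured in the same tissue, so dilution lowers them by the same fraction. A larger KM loss is an inference from the statement "Aminoglycosides do not concentrate effectively in tissues and remain mostly extracellular", set against the description of RIF as entering cells well. But extracellular drug includes drug in interstitium and plasma, which lavage does not directly rinse. Section 4.5 (Study Agents) also reports an aminoglycoside uptake receptor on type II pneumocytes, and gives no epithelial lining fluid figure for RIF.
- **That 6 to 47% can be set against the planned 50%.** The first is a fall in lung concentration on assumed inputs. The second is a between-drug difference in a rate parameter for nodules, fitted to pooled concentration–time data. Several regions of normal lung are sampled, so a local lavage need not affect all of them.
- **That the lavage should be deleted.** No stated endpoint uses it, but section 3.1 compares sputum with tissue and section 4.5 discusses lining-fluid ratios, so an airway sample fits the study's interest. A limit on place and time is enough.

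**Conclusion.** The point holds as a conditional one. Section 3.3.2 permits lavage at ligation without excluding the lobe to be resected or requiring bronchus closure first. If it is done there before closure, it can dilute or rinse uninvolved lung and open cavities but not closed nodules directly. It could thus distort comparisons referenced to lung, and nodules versus cavities, in the subjects concerned.

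How often this would happen and how large it would be cannot be derived from the document. The 6 to 47% rests wholly on assumed volumes, recovery, tissue mass and even mixing; its upper end combines the least favourable value of each range. The power figures assume lavage in every subject and a simple 1/(1 − d) scaling. A false RIF–KM difference is not established, since it would need unequal loss between the drugs. The change is worth making because it is cheap and an unrecorded lavage cannot be corrected afterwards.

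**What to change.** In section 3.3.2, allow the optional research lavage only after the bronchus of the resected lobe is closed, or only in a lobe that is not being resected. Record on the case report form whether it was done, the lobe, the time relative to bronchus ligation, and the volumes put in and recovered. Flag any specimen lavaged before closure, so that its lung and cavity values can be excluded in a sensitivity analysis of the primary endpoint and secondary endpoint 2.

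The cost is about one sentence of protocol text, a few recorded items, and slightly less freedom over an optional sample that no stated analysis uses.
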